### Patient recruitment and potential problems with compliance

The districts we have selected have very high malaria transmission intensity. In many malaria clinical trials recruitment rates of 5-7 caregivers per day has been demonstrated. Based on mobile phone ownership data, 50-65 % of the population is likely to own a mobile phone. So we anticipate recruiting 2-3 caregivers per day per site. Patients attending the outpatient department will be screened for eligibility criteria and those eligible will be randomized into the intervention and control arms as well as the adherence measurement categories. While recruitment at the four sites is cumulative we will try to ensure that participants at each of the four sites are as to close to equal as possible (approximately 500 participants per site). Potential challenges related to mobile phone and SMS use such as sharing of personal phones or not charging or switching off phones were determined during phase I and, if widely common, will be reinforced by the health workers to sensitize caregivers about the need to have mobile phones on and charged during the trial period.

### Quality control and limitation of bias

The major source of bias in adherence studies is reliance on participant recall and the possibility of false reporting. We have adopted an innovative approach of measuring adherence on different days during the dosing period, which is likely to reduce recall bias for the doses on days 1 and 2 in category 1 and 2 but not in category 3. The second primary outcome measure (day 3 post treatment review) requires objective assessment and we do not anticipate any biases in its measurement. The trial will be conducted under strict adherence to good clinical practice (GCP) standards.

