### Phase 2 – The randomized controlled trial

**Trial design:** Caregivers of eligible children with uncomplicated malaria will be randomly assigned (one to one) to two different arms: 1) the current standard of care based on provider counselling and health education alone, and 2) the current standard of care plus SMS reminders. Within each arm participants will be further randomly assigned to 3 different categories for the measurement of adherence to the different doses of AL. In the first category, 600 caregivers (300 per arm) will be visited at home on day 1 of follow up to measure adherence and timing of the second AL dose; in the second category, another 600 caregivers (300 per arm) will be visited at home on day 2 to measure adherence and timing of AL doses, 3 and 4, while, in the third category, a final 800 caregivers (400 per arm) will be reviewed at home on day 3 after they have completed the full treatment course to measure adherence for the full course of AL. All caregivers in each category will be visited at home only once to avoid biases in the subsequent measures of adherence as a result of the consultations at home. Caregivers in category 1 and 2 will be required to come to the health facility for the day 3 post treatment reviews, while those in category 3 will be visited at home on day 3.

AL will be administered according to weight bands: 5-14 kg, 1 tablet twice a day for three days, 15-24 kg, 2 tablets twice a day for three days and will be directly observed for the first dose, with the remaining 5 doses being provided for administration at home. All caregivers will receive standard instructions about how to administer AL at home and when to return to the facility for scheduled visits or immediately if unwell. At first dose administration, the telephone numbers of all eligible caregivers will be registered into the automated system by the randomizing nurse who will also observe directly supervised therapy of the first dose. The registration will record the time when the first dose is administered. A procedure for guiding the correct registration of the random number that will act as a unique identifier has been put in place (Figure 2).

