### Allocation of participants to trial groups

In order to ensure concealment of the intervention allocation to the trial staff, the randomization to the two study arms and subsequently to the 3 adherence measurement categories per arm was generated by an offsite statistician. Intervention allocation is concealed from the study staff reviewing the patients for treatment outcomes until evaluation is completed. However, such concealment could not be implemented for those conducting the home visits since they also collect data on SMS exposure, but we believe this lack of concealment will not affect the adherence outcome because the home visit will be conducted after the AL dose has been administered. Since caregivers will be visited at home only once, we will not measure adherence of the subsequent doses of AL in category 1 and 2. We designed the study to measure adherence to the full course of AL only in category 3 when all doses should have been completed to enable comparison with previous studies.

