### Primary outcomes

The first primary outcome will be adherence to a complete AL course (doses 2-6) measured in category 3 only and defined as: a) adherent, if they present with empty blister packs and report taking the medications as recommended (± 1 hour for dose 2 and ± 2 hours for doses 3-6); b) probably adherent if they do not present blister packs but report taking the medications as recommended, c) probably non adherent if they do not present blister packs and do not report taking the medications as recommended, and d) non adherent if they present blister packs with at least one tablet not used. The second primary outcome will be the proportion of patients reporting to the health facility for the day 3 post treatment review for the evaluation of clinical and parasitological cure at day 3 (only category 1 and 2).

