### Measurement of the efficacy of the SMS intervention on adherence

At each of the time points (day 1, 2 and 3); caregiver reports and pill counts will be used for measuring adherence in the intervention and control arms. While the day 1 and day 2 visits could result into slightly better adherence for doses, 3 and 4 because they are visited at home in the early days of follow up, category 3 will provide closer to real life adherence as these patients will only be visited at home after completion of the treatment course.

Measurement of the efficacy of the SMS intervention on day 3 post treatment reviews

At enrolment, all caregivers will be informed about the importance of a day 3 post treatment review from a clinical and drug resistance surveillance perspective, to confirm a malaria free status at day, or anytime during follow up if unwell for a period of 28 days. The proportion returning for the day 3 post treatment reviews will be determined in the intervention and control arms.

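### Every caregiver counted in the day-3 return outcome is due a home visit from unblinded staff one or two days before the appointment, and the plan considers the effect of visits for adherence but not for return

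*Protocol article*

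**What the plan says.** All references are to the protocol article.

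- **Outcome.** Primary outcomes: "The second primary outcome will be the proportion of patients reporting to the health facility for the day 3 post treatment review", restricted to categories 1 and 2.
- **Visits.** Phase 2 – The randomized controlled trial: "In the first category, 600 caregivers (300 per arm) will be visited at home on day 1 of follow up", and "another 600 caregivers (300 per arm) will be visited at home on day 2". Both categories are then expected at the facility on day 3, "while those in category 3 will be visited at home on day 3".
- **Effect of visits, as the plan sees it.** Same section: "All caregivers in each category will be visited at home only once to avoid biases in the subsequent measures of adherence". Measurement of the efficacy of the SMS intervention on adherence adds that doses 3 and 4 might be taken slightly better by families in categories 1 and 2, "because they are visited at home in the early days of follow up". It regards category 3 as nearer to ordinary practice, since that visit comes once treatment is over.
- **Blinding.** Allocation of participants to trial groups: "such concealment could not be implemented for those conducting the home visits since they also collect data on SMS exposure". The article considers this harmless for adherence because the dose has already been given when the visitor arrives.
- **Bias.** Quality control and limitation of bias says the second primary outcome "requires objective assessment and we do not anticipate any biases in its measurement".
- **Power.** Sample size estimation gives over 90% power with 600 per arm for a 10-point difference around a 45% return.

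**The concern.** The plan accepts that a staff visit can change what a family does afterwards. For adherence to the full course it deals with this by measuring in category 3, where the visit follows the last dose. For day-3 return the order is reversed: only pre-visited categories count, and the visit falls two days (category 1) or one day (category 2) before the behaviour being measured. The argument for accepting unblinded visitors, that the dose precedes the visit, cannot carry over to return, which follows the visit.

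At stake is what the day-3 result can mean. The comparator is described as counselling and health education alone. If the visit acts as a prompt, the control group for this outcome is counselling plus a visit, and the SMS effect is estimated on top of it. Visitors who know the arm and ask about messages could also, in principle, prompt the two arms differently. The article offers no assessment of either possibility; its bias section considers only how attendance is measured.

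**Working it through.** **1. Order of events**

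| Outcome | Where counted | Home visit relative to the behaviour |
|---|---|---|
| Full-course adherence | Category 3 | After the last dose |
| Day-3 return | Category 1 | Two days before |
| Day-3 return | Category 2 | One day before |

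Category 3 is reviewed at home, so no group shows facility return without a prior visit. A no-visit SMS effect on return cannot be estimated from this design.

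**2. The plan's own power**

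Inputs: 600 per arm, a 10-point difference and 45% (Sample size estimation), taken as 45% versus 55%. The 0.05 level is stated there for the first primary outcome; it is applied here and assumed two-sided. Missing day-3 data count as not returning (Trial Data Analysis), so 600 per arm stay in the denominator.

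Power = Φ[(d − 1.96·SE0)/SE1], where d = p2 − p1, p̄ is the mean of the two proportions, SE0 = √(2p̄(1 − p̄)/600) and SE1 = √((p1(1 − p1) + p2(1 − p2))/600).

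- SE0 = √(2 × 0.25/600) = 0.02887
- SE1 = √((0.2475 + 0.2475)/600) = 0.02872
- z = (0.10 − 0.05658)/0.02872 = 1.512, so power is 93.5%

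The stated figure of over 90% is reproduced.

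**3. Illustration of an equal visit effect**

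The documents give no size for a visit effect. Assume the visit brings back a share f of would-be non-returners in both arms, independently of SMS, and that 45% and 55% are rates without a visit. Then control return is 0.45 + 0.55f, SMS return is 0.55 + 0.45f, and the difference is 0.10(1 − f).

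| f (assumed) | Control | SMS | Difference | Power |
|---|---|---|---|---|
| 0 | 45.0% | 55.0% | 10 points | 93.5% |
| 0.1 | 50.5% | 59.5% | 9 points | 88.1% |
| 0.2 | 56.0% | 64.0% | 8 points | 80.8% |
| 0.3 | 61.5% | 68.5% | 7 points | 72.0% |

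For f = 0.2: SE0 = √(2 × 0.24/600) = 0.02828, SE1 = √((0.2464 + 0.2304)/600) = 0.02819, z = (0.08 − 0.05544)/0.02819 = 0.871, power 80.8%.

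**4. Illustration of unequal prompting**

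Suppose SMS had no effect but visits raised return in one arm only, from 45%. With the same formula, the chance of a significant result in that direction would be about 10%, 18% or 41% for a rise of 2, 3 or 5 points, against 2.5% nominal. Nothing in the article indicates that this will happen.

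**5. Could a comparison of categories 1 and 2 settle it?**

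With 300 per arm in each category and return near 50%, the standard error of the arm-by-category contrast is √(4 × 0.25/300) = 0.0577, or 5.8 points. For 80% power the contrast would have to be (1.96 + 0.84) × 5.8 ≈ 16 points. It also compares a one-day with a two-day gap, not visited with unvisited.

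**The case against.** The strongest reply has four parts.

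First, the bias statement refers to measurement, in a paragraph about recall and false reporting. Attendance suffers from neither, and staff reviewing treatment outcomes are kept unaware of the arm. This stands. A reader might infer that the statement is false; it is not, but it leaves out a different route of influence.

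Second, both arms are scheduled for the same single visit at the same times, and category is randomised within arm. An equal visit effect therefore does not invalidate the comparison. This stands too. A reader might infer that the day-3 result will be biased, but that needs visitors to act differently by arm, which the documents do not show.

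Third, the article describes the visit as caregiver reports, pill counts and questions on SMS exposure. It does not say that the appointment is mentioned, and visit scripts are often left to a fuller protocol. So a missing script is not an error in itself, and the visit cannot be called a reminder as a fact. What remains is that the plan itself thinks visits may shift later behaviour.

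Fourth, the power figures rest on assumptions. The article calls 45% conservative without saying whether a prior visit is included; if it is, the dilution table does not apply. Questions about SMS might also draw attention to the messages and enlarge the contrast. Even at f = 0.2, power is 81%, about the 80% accepted for the first primary outcome. This stands: the documents do not show that the trial is underpowered or that a null result would be uninterpretable.

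**Conclusion.** The point holds as a gap in reasoning and a limit on interpretation. All caregivers in this primary outcome are due an unblinded home visit before the behaviour is observed. The stated defence of unblinded visits covers adherence and not return, and the bias section covers measurement only. The visit may be a co-intervention that dilutes the SMS effect, and unequal prompting by arm is possible but not shown.

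The randomised comparison remains valid if visits act equally in both arms. What it then estimates is the SMS effect among caregivers who were also visited, not SMS against counselling alone.

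The size is unknown. The figures of 88%, 81% and 72% are illustrations that depend on an assumed visit effect, equal in both arms and independent of SMS, and on 45% and 55% being no-visit rates.

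**What to change.** 1. Use one identical, neutral script for the day-1 and day-2 visits in both arms, in which the visitor does not raise the day-3 review. Questions from caregivers may be answered in the same standard way in both arms. Overall study design says the trial began in June 2014, so if recruitment is under way, bring the script in for both arms together and record the date.
2. Amend Allocation of participants to trial groups to say that the argument about concealment does not extend to day-3 return. Amend Quality control and limitation of bias to say that attendance is objectively recorded but may be influenced by the preceding visit. State the conclusion as the SMS effect among caregivers who also received a home visit, not against counselling alone.
3. Optionally, report return by arm within categories 1 and 2 as description only. It cannot estimate a no-visit effect and has little power.

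The cost is a small procedural change, which if made mid-trial alters the visit partway through recruitment, and a narrower conclusion. Sample size and visit schedule are unchanged.

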### Inclusion criteria

Caregivers of male and female children aged <5 years old; body weight eligibility for AL; microscopically confirmed, mono-infection of *Plasmodium falciparum* (parasitaemia ≥ 500/μL to 200,000/μL); history of fever in the last 24 hours or presence of fever (axillary temperature ≥ 37.5°C); network coverage at patients’ household; owning a mobile phone or having shared access to a mobile phone in household; ability to access a mobile phone on a daily basis for the period of follow up; ability to open and read SMS or presence of someone in the household who can open or read an SMS and written informed consent.

### Exclusion criteria

Caregivers not owning a mobile phone; and have no shared access to any phone in the household; patients with severe malaria; danger signs: not able to drink or breast-feed, vomiting (>twice in 24 hours), recent history of convulsions (>1 in 24 h), unconscious state, unable to sit or stand; presence of concomitant illness or any condition which in the judgement of the investigator would place the subject at undue risk or interfere with assessment; severe malnutrition (weight for height<70% of the median NCHS/WHO reference); ongoing prophylaxis with drugs having antimalarial activity such as cotrimoxazole for the prevention of pneumocysti carini pneumonia in children born to HIV+ women; having taken AL in the previous one month and having participated in the current trial.

### Sample size estimation

The sample size estimation was based on the first primary outcome-adherence to the full course of AL treatment. Assuming a malaria treatment adherence of 65% with the current standard of care alone [30], a sample size of 400 participants in category 3 per arm will be able to detect a minimum desirable effect difference of 10% with 80% power at a 0.05 level of significance, assuming a 15% loss to follow up. In order to robustly measure adherence to the individual AL doses, we have included an additional 300 caregivers per arm in each of the first and second categories. This sample size will be sufficient to detect an effect difference of 10% around an estimated adherence of 75% to the individual AL doses, assuming a 10% loss to follow up. For the measurement of the day 3 post-treatment reviews, the combined sample size in categories 1 and 2 (600 per arm), has adequate power (over 90%) to detect a 10% effect difference around a conservative estimate of the proportion returning for day 3 post-treatment review of 45%. Therefore, we will recruit a total 1,000 caregivers for the study.

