### Trial Data Analysis

Individual patient level pooled analysis of the data from the four sites will be conducted, according to CONSORT standards for reporting RCTs. A random effects model will be used to adjust for site and other covariates. To analyse for effect differences for the primary outcomes, intention to treat (ITT) principles will be used and additional sensitivity and per protocol (PP) analyses will be conducted separately. ITT implies that all randomised patients will be considered in the outcomes as per randomization. Missing data will be imputed as intervention failure (non-adherent or not report for post treatment review), using multiple imputation for missing data not directly related to adherence. The latter is considered the gold standard for handling missing data as it leads to unbiased estimates and standard errors compared to single imputation methods [31]. In the per protocol (PP) analysis, only patients completing the study and have been exposed to the intervention will be included. Category analyses will be conducted to investigate the relationship between adherence and treatment success (clinical and parasitological cure) at day 3. The study is powered adequately, so no interim analyses will be conducted.

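### The 80% power for full-course adherence holds only if lost participants are excluded; with missing counted as non-adherent, the natural reading of the ITT analysis, it is about 69%

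*Protocol article*

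**What the plan says.** The sample size section of the protocol article rests on the first primary outcome, adherence to the full AL course in category 3. Its inputs are "Assuming a malaria treatment adherence of 65% with the current standard of care alone", "a sample size of 400 participants in category 3 per arm" and "assuming a 15% loss to follow up", and it claims that this number "will be able to detect a minimum desirable effect difference of 10% with 80% power at a 0.05 level of significance".

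The abstract names intention-to-treat as the primary analysis. The Trial Data Analysis section defines this as counting every randomised patient in the arm assigned, and then states: "Missing data will be imputed as intervention failure (non-adherent or not report for post treatment review". The same sentence goes on to mention multiple imputation, limited to missing data not directly tied to adherence. The next sentence says of that method: "The latter is considered the gold standard for handling missing data as it leads to unbiased estimates and standard errors compared to single imputation methods".

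**The concern.** The two sections treat the same lost participants differently. Inflating a sample size for loss is the right correction when lost participants leave the analysis: fewer people are analysed, but the rates are unchanged. When lost participants are kept and scored as non-adherent, the denominator stays whole and the rates shrink. Equal loss in both arms then multiplies the true difference by one minus the loss rate. An allowance made for the first situation does not protect power in the second.

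At stake is the power of the primary analysis of the first primary outcome, at the loss rate the protocol itself plans for. The estimate from that analysis would also be a diluted version of the 10-point difference used in the design.

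**Working it through.** **Inputs.** Control adherence 65%, difference 10 points (so 75%), 400 per arm, 15% loss and alpha 0.05 come from the sample size section. The 1:1 allocation comes from the trial design ("will be randomly assigned (one to one) to two different arms"). Sidedness is not stated. Two-sided is assumed, because one-sided versions give 305 per arm after inflation (329 with continuity correction) and do not reproduce 400.

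**Formulas** (two proportions, pooled variance under the null, p̄ = (p1 + p2)/2):

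- n = [1.96·√(2p̄(1−p̄)) + 0.842·√(p1(1−p1) + p2(1−p2))]² / (p1 − p2)²
- power = Φ{ [ |p1 − p2| − 1.96·√(2p̄(1−p̄)/n) ] / √[(p1(1−p1) + p2(1−p2))/n] }

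**Step 1: reproduce the plan's figure.** For 0.65 against 0.75, p̄ = 0.70:

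- n = [1.96 × 0.6481 + 0.842 × 0.6442]² / 0.01, which rounds up to 329 evaluable per arm.
- Inflated for loss: 329 / 0.85 = 388, close to the stated 400. With continuity correction it is 349, inflated to 411.
- Evaluable after 15% loss: 400 × 0.85 = 340.
- Power on 340 = Φ[(0.10 − 0.0689) / 0.0349] = Φ(0.89) = 81.3% (79.0% with continuity correction).

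The stated 80% is reproduced, with the lost 15% removed and the rates undiluted.

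**Step 2: apply the stated primary analysis.** Score the 15% as non-adherent in each arm and keep all 400:

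- Control: 0.65 × 0.85 = 0.5525.
- Intervention: 0.75 × 0.85 = 0.6375.
- Difference: 0.085; p̄ = 0.595.
- Power = Φ[(0.085 − 0.0680) / 0.0346] = Φ(0.49) = 68.8% (66.2% with continuity correction).

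**Step 3: what would restore 80%.** Either about 523 per arm in category 3 for a true 10 points, or a larger true effect at 400 per arm. A true 11.4 points gives 0.764 × 0.85 = 0.6494 against 0.5525, and power of 80.0%.

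**Step 4: vary the loss, equal in both arms, 65% against 75% among those observed.**

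| Loss | Rates compared | Power, missing = non-adherent (400 per arm) | Power, lost excluded |
|---|---|---|---|
| 5% | 61.75% vs 71.25% | 81.4% | 85.4% |
| 10% | 58.5% vs 67.5% | 75.2% | 83.5% |
| 15% | 55.25% vs 63.75% | 68.8% | 81.3% |
| 20% | 52.0% vs 60.0% | 62.6% | 79.0% |

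**The case against.** **The missing-data sentence can be read another way.** Its multiple-imputation clause could describe the reason for missingness, so that an outcome missing for a reason unconnected with adherence, such as a household that could not be found, would be multiply imputed. The primary analysis would then already do part of what is asked. The wording is awkward enough to need clarifying. The reading is strained, though, because the failure rule names non-adherence explicitly as the imputed value.

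**The 65% and 75% might already count lost caregivers as non-adherent.** Then 400 per arm would give 87.1% power. The source of the 65% is not available here, so this cannot be excluded. It fits poorly with the plan: no loss allowance would be needed, and 400 is reproduced only with one.

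**Loss may turn out smaller.** This is correct, and at 5% the shortfall disappears. But 15% is the protocol's own planning figure.

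**Counting missing as failure is a recognised conservative rule.** It is, and with equal loss and no true effect it keeps the nominal type I error. The rule need not be abandoned; the power statement has to match it.

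Four stronger readings are tempting, and the documents do not support them:

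- *The sample size contains an arithmetic error.* It does not, since the figure reproduces. The fault is a mismatch with the analysis.
- *The dose-level outcomes are underpowered in the same way.* The protocol states no power for them, calls the size only sufficient, and does not fix the pair of rates compared.
- *Unequal loss will bias the result or raise the false-positive rate.* No arm-specific loss is given, so any such figure is illustrative. For example, under a true 10-point effect, 15% loss in control and 10% in intervention would give 95% power; the reverse would give 33%.
- *Every missing category 3 outcome is a failed home visit that carries no information on adherence.* The protocol does not say what makes up the 15%. An outcome could be incomplete after a completed visit, and absence could itself be related to non-adherence.

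**Conclusion.** The point stands as a mismatch between the sample size section and the Trial Data Analysis section. The 80% claim is true for an analysis that excludes the lost 15%. For the primary analysis as most naturally read, power at the planned loss is about 69%, roughly 11 points below the stated figure.

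This rests on four assumptions: a two-sided 0.05 test, equal loss of 15% in both arms, 65% and 75% being rates among observed caregivers, and missing category 3 adherence being scored as non-adherent. The first three are not stated outright but agree with how 400 is reproduced. The fourth is the natural reading of a sentence that should be clearer.

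**What to change.** 1. Rewrite the missing-data sentence in Trial Data Analysis so that it says, separately for category 3 adherence, the day 3 review and other variables, which imputation rule applies in the primary analysis.
2. If failure imputation stays primary for category 3 adherence, restate the sample size section: about 69% power for a true 10-point difference with 15% loss in each arm, or 80% power for about 11.4 points. Add a pre-specified multiple-imputation sensitivity analysis of category 3 adherence.
3. Alternatively, make multiple imputation primary for category 3 adherence and keep failure imputation as the sensitivity analysis. This relies on data being missing at random, which cannot be tested and which statisticians may dispute, so it is an option rather than an automatic repair.
4. Keep non-return scored as failure for the day 3 facility review, where non-return is the outcome itself.

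The cost is revised wording and one additional analysis, plus a less favourable power statement if failure imputation is kept. No further participants are required.

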**Methods/Design:**

A “proof of concept” open label randomised controlled trial will be conducted at four sites in Western Kenya. Principal research questions are: 1) Can mobile phone SMS reminders improve patient adherence to malaria treatment? 2) Can mobile phone SMS reminders improve day 3 post treatment reviews? Eligible caregivers (n=1000 per arm) of children under five years old with uncomplicated malaria will be randomly assigned (one to one) to: a) the current standard of care (provider counselling and health education); and b) the current standard of care plus SMS reminders. Within each arm, caregivers will be further randomized to three different categories. In categories 1 and 2, 300 caregivers per arm per category will be visited at home on day 1 and 2 of follow up respectively, to measure appropriate timing and adherence of the second Artemether-Lumefantrine (AL) dose and doses 3 and 4. Further, caregivers in categories 1 and 2 will be required to come to the health facility for the day 3 post treatment reviews. Finally, in category 3, 400 caregivers per arm will be visited at home on day 3 to measure adherence for the full AL course. Each category will be visited at home only once to avoid biases in the measures of adherence as a result of home consultations. Primary outcomes will be adherence to the full AL course (category 3), as well as, the proportion of patients reporting back for day 3 post treatment reviews (categories 1 and 2). The primary analysis will be intention-to-treat. Costs of the intervention will be measured over the period of the intervention, and a cost-effectiveness ratio will be estimated.

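### The sample-size section closes with a total of 1,000 caregivers, but every other size in the article gives 1,000 per arm, 2,000 in total; most likely the words 'per arm' were dropped

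*Protocol article*

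**What the plan says.** The last sentence of Sample size estimation reads: "Therefore, we will recruit a total 1,000 caregivers for the study".

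The other statements of size in the article are:

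- **Abstract, Methods/Design:** "Eligible caregivers (n=1000 per arm) of children under five years old with uncomplicated malaria", randomised one to one.
- **Phase 2, trial design:** "In the first category, 600 caregivers (300 per arm) will be visited at home on day 1"; "another 600 caregivers (300 per arm) will be visited at home on day 2"; and "a final 800 caregivers (400 per arm) will be reviewed at home on day 3". Participants "will be randomly assigned (one to one) to two different arms".
- **Patient recruitment:** "approximately 500 participants per site", with four sites.
- **Sample size estimation, before its last sentence:** 400 per arm in category 3, a further 300 per arm in each of categories 1 and 2, and 600 per arm in categories 1 and 2 combined for the day 3 review.

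The figure 2,000 is not written anywhere as the total. The reader has to add it up.

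**The concern.** The sentence is worded as the conclusion of the per-arm figures before it, yet it gives half their sum. It is also the only place where the article states one overall enrolment figure. A reader who goes to the sample-size section for the planned size, for example to judge recruitment or to compare the published trial with its protocol, would take away the wrong number.

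What is at stake is which total the power statements belong to. They cannot be true of both 1,000 and 2,000. The Trial Data Analysis section also justifies having no interim analysis by the study being adequately powered, so that justification depends on the same total.

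**Working it through.** **1. The total.** Inputs are the category and site sizes listed above.

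| Source | Arithmetic | Total |
|---|---|---|
| Sample size estimation, per-arm figures | 2 × (400 + 300 + 300) | 2,000 |
| Abstract | 2 × 1,000 | 2,000 |
| Phase 2, trial design | 600 + 600 + 800 | 2,000 |
| Patient recruitment | 4 × about 500 | about 2,000 |
| Sample size estimation, last sentence | stated | 1,000 |

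The stated categories do not fit into 1,000. Category 3 alone takes 800, which leaves 200 for two categories that need 600 each.

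**2. Do the component sizes reproduce?** The article does not say whether the 0.05 level is one- or two-sided. I assume two-sided, z = 1.960, with z = 0.8416 for 80% power. The size per arm, with p̄ the mean of the two proportions, is

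n = [1.960·√(2p̄(1−p̄)) + 0.8416·√(p₁(1−p₁) + p₂(1−p₂))]² / (p₂−p₁)²

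and loss to follow-up d is allowed for by n/(1−d).

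- *Category 3*, 65% vs 75%, 15% loss: (1.960 × 0.6481 + 0.8416 × 0.6442)² / 0.01 = 329 per arm, and 329/0.85 gives 388. With continuity correction the figures are 349 and 411. The stated 400 lies between 388 and 411.
- *Categories 1 and 2*, individual doses, read as 75% vs 85%, 10% loss: 250 per arm, 278 after loss. With continuity correction, 270 and exactly 300, the stated figure. The article gives no power for this comparison; 80% is assumed.

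**3. Power at each total.** The formula is

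power = Φ{ [(p₂−p₁)√n − 1.960·√(2p̄(1−p̄))] / √(p₁(1−p₁) + p₂(1−p₂)) }

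*Category 3, full-course adherence, 65% vs 75%.*

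- Total 2,000: 400 × 0.85 = 340 evaluable per arm. (0.1 × 18.439 − 1.2702)/0.6442 = 0.891, so power is 81%. The article claims 80%.
- Total 1,000, categories halved: 200 × 0.85 = 170 per arm. (0.1 × 13.038 − 1.2702)/0.6442 = 0.052, so power is 52%.

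*Day 3 review, 45% vs 55%.* The article attaches no loss allowance to this outcome.

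- Total 2,000: 600 per arm. (0.1 × 24.495 − 1.3859)/0.7036 = 1.512, so power is 93%. The article claims over 90%.
- Total 1,000, categories halved: 300 per arm. (0.1 × 17.321 − 1.3859)/0.7036 = 0.492, so power is 69%.

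The article's own power statements therefore go with 2,000 and not with 1,000. The halving in the 1,000 rows is my assumption, made only to show which total the claims fit.

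**The case against.** The strongest reply is that this is a slip of wording that any careful reader can repair. The number 1,000 is exactly right per arm, the sentences just before it use per-arm figures, and three other sections agree on 2,000. The allocation to arms and categories had already been generated by an offsite statistician, and the trial had started in June 2014. The working target would come from the allocation list and the full protocol, not from this sentence. All of that stands, and it fixes the nature of the error: a misstated total, most likely a missing 'per arm'.

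It does not remove the error. The sentence says the number is a total for the study, and nothing in the article corrects it.

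A reader might infer more: that recruitment will stop at 1,000, or that both primary outcomes are underpowered. The documents support neither. No section makes 1,000 a stopping target. The oversight section has the Data Monitoring Board follow recruitment rates and names no number. The site targets point to 2,000. At the sizes the design sets out, the stated power reproduces.

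Power under the rule that scores missing outcomes as failures is a separate question. It would lower power for adherence at either total, so it should not be counted as an effect of this sentence.

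**Conclusion.** The point holds as an internal contradiction: the stated total is wrong by a factor of two, and the article's own figures settle it at 2,000 (1,000 per arm). That conclusion is addition and needs no statistical assumption.

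The power figures (about 81% and 93% at 2,000, against 52% and 69% at 1,000) rest on a two-sided 0.05 test, the normal approximation, the article's planning proportions with the 10-point difference taken upwards, and, for the lower pair, a proportional halving that nobody plans. They show which total the power claims belong to. They are not a forecast of the trial's power.

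The correction should be made, because the overall sample size is a figure that readers rely on and this is the only sentence that states it.

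**What to change.** Replace the last sentence of Sample size estimation with: *We will recruit 1,000 caregivers per arm, 2,000 in total (300, 300 and 400 per arm in categories 1, 2 and 3).*

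The cost is one sentence. Design, allocation and analysis do not change. As a precaution only, the sponsor can confirm that the recruitment target in use is 2,000; nothing in the article suggests that it is not.
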